## Abstract

**Background:** This proposal aims to explain some of the gaps in scientific knowledge on the natural history of coronavirus disease (COVID-19), with a specific focus on immune, inflammatory, and metabolic markers, in parallel with temporal assessment of clinical and mental health in patients with COVID-19. The study will explore the temporal modulatory effects of physical activity and body composition on individual trajectories. This approach will provide a better understanding of the survival mechanisms provided by the immunomodulatory role of physical fitness. **Methods:** We will conduct a prospective observational cohort study including adult patients previously infected with the SARS-CoV-2 virus who have expressed a mild to moderate COVID-19 infection. Procedures will be conducted for all participants at baseline, six weeks after vaccination, and again at 12 months. At each visit, a venous blood sample will be collected for immune phenotypic characterization and biochemistry assays (inflammatory and metabolic parameters). Also, body composition, physical activity level, cardiovascular and pulmonary function, peripheral and respiratory muscle strength, functional exercise capacity, and mental health will be evaluated. Using the baseline information, participants will be grouped based on physical activity levels (sedentary versus active), body composition (normal weight versus overweight or obese), and SARS-CoV-2 status (positive versus negative). A sub-study will provide mechanistic evidence using an in-vitro assay based on well-trained individuals and age-matched sedentary controls who are negative for SARS-CoV-2 infection. Whole blood will be stimulated using recombinant human coronavirus to determine the cytokine profile. Peripheral blood mononuclear cells (PBMCs) from healthy well-trained participants will be collected and treated with homologous serum (from the main study; samples collected before and after the vaccine) and recombinant coronavirus (inactive virus). The metabolism of PBMCs will be analyzed using Respirometry (Seahorse). Data will be analyzed using multilevel repeated-measures ANOVA. **Conclusions:** The data generated will help us answer three main questions: (1) Does the innate immune system of physically active individuals respond better to viral infections compared with that of sedentary people? (2) which functional and metabolic mechanisms explain the differences in responses in participants with different physical fitness levels? and (3) do these mechanisms have long-term positive modulatory effects on mental and cardiovascular health? Trial registration number: Brazilian Registry of Clinical Trials: RBR-5dqvkv3. Registered on 21 September 2021.

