Considering the previous rationale and the current pandemic, it is imperative to ask: What are the long-term consequences of COVID-19 and how do physical activity, body composition, immune profiles, and inflammation contribute to different trajectories of general clinical functions throughout a lifetime and overall physiological recovery? There is no data on the prevalence, nature, and behavior of COVID-19 in physically active individuals, and little is known about the long-term health consequences of COVID-19 and its relation with SARS-CoV-2 vaccination [28].

This proposal describes methods for an observational prospective follow-up investigation of adult patients previously infected with mild to moderate COVID-19, we will conduct measures 3 times, (1) baseline, (2) six weeks after full vaccination, and (3) again at 12 months. Investigations of this magnitude in individuals who previously had mild to moderate SARS-CoV-2 infection are relevant for generating data in a population that is non-severely affected by the disease, and who may suffer from sequelae that are yet to be explored, with the intention to assist in the planning of rehabilitation programs.

As is known, age and metabolic disorders are factors related to poor prognostic of the COVID-19 disease. Our idea will be to study a sub-population that exhibits low risk of severe COVID-19 disease, and that in general will be not admitted to the hospital in intensive care. However, the consequences of infection during the long term were never studied.

Our main objective is to evaluate if physical activity levels and the number of adipose tissue depots are determinants of systemic inflammatory response and general clinical functions in adults who previously suffered from mild to moderate COVID-19, before and after specific vaccination, using a cohort prospective observational study. Additionally, we will explore modulatory effects of physical activity on immune responses to the virus, focusing on the function and metabolism of peripheral blood mononuclear cells (PBMCs) after in vitro exposure to homologous serum and/or recombinant coronavirus.

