At each visit, body composition will be assessed using Dual X-ray Absorptiometry (DXA), bioimpedance, and ultrasonography. Accelerometers will be used to assess habitual physical activity. The cardiovascular function will be evaluated using an electrocardiogram, Doppler echocardiogram, and heart rate variability. The pulmonary function will be evaluated by spirometry. Peripheral and respiratory muscle strength will be measured using an electronic dynamometer and manovacuometer. Functional exercise capacity will be assessed using the 6-min walk test (6MWT). Mental health will be evaluated using questionnaires. Venous blood samples will be collected for immune phenotypic characterization and biochemistry assays (inflammatory and metabolic parameters). A protocol for ex vivo stimulation of whole blood with LPS will be used to imitate an inflammatory environment for determining the level of cytokines. Serum markers and markers of early cardiovascular function will be correlated with body fat and physical activity levels. Flow cytometry will be conducted and monocytes, T cells, and Natural Killer cell subsets in whole blood will be quantified and characterized. Additionally, after characterization and correlation of the determinants of SARS-CoV-2 severity with the amount of body fat and physical activity level and based on the hypothesis that individuals with low body fat and high physical activity levels have a better clinical outcome, we will examine immune cells from well-trained subjects (higher physical activity level and low-fat body) using an in vitro experimental model and compare them with age-matched non-trained subjects (control model).

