Body composition (total fat mass, trunk fat mass, abdominal fat, and lean mass) will be analyzed by ultrasonography using a 3.5-MHz probe located 1 cm from the umbilicus. Two ultrasonography measurements of visceral adipose tissue will be defined as the distance between the internal face of the same muscle and the anterior wall of the aorta. All measurements will be expressed in absolute and percentage values. Participants will be grouped into those with low-visceral adipose tissue (values below 3 ± 1 cm) and those with high-visceral adipose tissue (values above 5 ± 1 cm). Also, body composition (body mass, fat mass, musculoskeletal, bone, and fat-free mass from upper and lower limbs and trunk) will be analyzed using DXA (model DPX-MD, software 4.7, General Electric Healthcare, Lunar DPX-NT; Little Chalfont, Buckinghamshire, United Kingdom). Impedance measurements will be taken using a phase-sensitive bioimpedance analyzer (Bia Vitality, Harrisville, NH, USA) at a frequency of 50 kHz. Bioimpedance parameters [Resistance (R) and reactance (Xc)] were analyzed based on the BIVA procedures [33]. Phase angle will be calculated as the arctangent of Xc/R*180°/π. Total, intra- and extracellular water, body cell, and muscle mass will be estimated using specific bioimpedance-derived equations [34,35,36].

Nutritional information will be recorded at the initial screening from three-day food diaries that will be filled over two weekdays and one weekend day to better reflect typical intakes. Participants will meet with a nutritionist before testing and they will be instructed on how to complete the food diaries. Total energy, protein, carbohydrates, and fat intake will be analyzed using NutWinsoftware, version 1.5.

Physical activity levels will be measured using a triaxial accelerometer (GT3X+; ActiGraph, LLC, Pensacola, FL, USA) which gives valid estimates of physical activity in controlled and free-living environments. Participants will use an accelerometer worn above the waist for seven consecutive days during waking hours. A minimum of four days with at least 10 h/day will be defined as valid accelerometer data. Participants will be instructed not to use the accelerometer while bathing or performing water activities. Each day, participants will be responsible for recording when they went to sleep, when they woke up, and whether or not they took off the device. The data will be processed using the ActLife software version 6.9.2 (Pensacola, FL, USA).

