### 2.10. Sample Size Estimation and Planning for Data Analysis

A Cohort of participants previously infected with SARS-CoV-2 and age-matched healthy participants will be randomly selected from the target population. Sample size calculation (G*Power, version 3.0; power = 0.80; α level = 0.05; medium-size effect) provided an estimated 75 participants. Therefore, 100 male and female participants aged 20–40 years will be recruited (over-recruitment compensates for dropouts during follow-up).

Participants will be stratified based on habitual physical activity levels (assessed by accelerometry-low versus normal physical activity levels), body composition (normal weight versus overweight or obese), and SARS-CoV-2 status (positive versus negative). In addition, a sub-analysis will be stratified based on sex (men vs. women).

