## 3. Discussion

This protocol describes an ambitious follow-up study that will be conducted in adults previously infected with COVID-19 (before and after vaccination program), highlighting long-term consequences of COVID-19 and its correlation with physical activity, body composition, and cross-linked with vaccination in the Brazilian population. Our hypothesis links reduced visceral adipose tissue deposits (which exhibit an anti-inflammatory profile, as hypoleptinemia and hyperadiponectinemia) with higher physical activity levels as central factors in reducing the severity of SARS-CoV-2 aggression, promoting metabolic programming of immune cells (favoring anti-inflammatory response), protecting the cardiovascular system, and general clinical profile.

Patients with COVID-19 who were consistently inactive and malnutrition had a greater risk of hospitalization, admission to the ICU, and death due to COVID-19 compared with patients who were consistently meeting the minimum physical activity guidelines (150 min/week) [27,47,48]. Longitudinal cohort studies of individuals who developed severe COVID-19 are being conducted to investigate possible symptoms and long-term clinical and functional alterations [49,50]. Longitudinal follow-up studies reporting persistent symptoms and sequelae of COVID-19 in mild and moderate patients are also needed in order to understand the intrinsic physiological mechanisms involved in these processes, their potential protective factors, and public health policies needed for treatment in the post-pandemic period in order to substantially minimize long-term chronic sequelae.

In addition to investigating an overlooked population, one advantage of the study proposed here is that we will conduct comprehensive symptom and clinical assessments of long-COVID manifestations pre- and post-vaccination. Potential limitations include the fact that we will rule out the presence of current re-infection based only on the absence of clinical signs and symptoms, rather than on the basis of a negative RT-PCR test. We will also only assess a specific, young population.

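### Physical activity is measured continuously in everyone but planned as a two-group factor, under two label pairs that do not match; a continuous term would keep a third to a half of the information that the split discards

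*Protocol article*

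**What the plan says.** The main objective, at the end of Section 1, is to "evaluate if physical activity levels and the number of adipose tissue depots are determinants of systemic inflammatory response" and general clinical functions. Activity and adiposity therefore share the role of exposure.

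Section 2.2 measures activity with a triaxial accelerometer worn for seven days. The only rule it gives concerns wear time: "A minimum of four days with at least 10 h/day will be defined as valid accelerometer data".

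The grouping is then stated twice:

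- Abstract: from the baseline information, "participants will be grouped based on physical activity levels (sedentary versus active"), with body composition and SARS-CoV-2 status as the other factors.
- Section 2.10: stratification on "habitual physical activity levels (assessed by accelerometry-low versus normal physical activity levels"), with the same two other factors.

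The only model named for the data is the multilevel repeated-measures ANOVA in the Abstract. Section 2.1 adds an analysis in which activity is not described as grouped: "Serum markers and markers of early cardiovascular function will be correlated with body fat and physical activity levels".

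The in-vitro sub-study has its own comparator. The Abstract describes "well-trained individuals and age-matched sedentary controls who are negative for SARS-CoV-2 infection". Section 2.1 says the investigators will "compare them with age-matched non-trained subjects (control model"), and Section 2.3 also calls the controls non-trained.

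**The concern.** There are two linked problems.

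First, the two label pairs describe different contrasts on their face. Normal is a weaker upper class than active, so low against normal need not be the same comparison, or have the same expected effect, as sedentary against active. The article does not say that they are synonyms. A later document that fixes one grouping will have to depart from the wording of either the Abstract or Section 2.10.

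Second, whichever pair is meant, a two-level factor treats everyone on the same side of the cut as equally exposed. The stated hypothesis is graded (Section 3 speaks of higher activity levels) and the instrument gives a graded measurement. Precision for one of the two main exposures is therefore given up by choice, in a study that plans on only 75 evaluable people out of 100 recruited and splits them on two further factors.

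**Working it through.** **1. The plan's own figure.** Section 2.10 gives power 0.80, α 0.05, a medium effect and 75 participants. It does not give the test, the number of groups or visits in the calculation, or the within-person correlation, so 75 cannot be derived from the stated inputs alone.

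| Calculation | Two-sided | One-sided |
|---|---|---|
| Two groups, standardised difference 0.5 | 128 in total | 102 in total |
| Correlation of 0.3 | 85 | 68 |

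Figures at or near 75 appear only under unstated choices. For example, a group-by-visit interaction with effect size f = 0.25, eight groups, three visits and within-person correlation 0.3 gives 75. What follows is therefore not a recalculation of the plan's power.

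**2. Information kept by a split.** Assume activity X is normal and its relation to the outcome is linear. Cut X so that a share p falls in one group, let z_p be the cut on the standard normal scale and φ the normal density. The correlation with the outcome is then multiplied by

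a = φ(z_p) / √(p(1−p)),

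and the share of information kept is a².

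| Split (assumed) | φ(z_p) | a | Kept, a² | Lost |
|---|---|---|---|---|
| 50/50 | 0.399 | 0.798 | 0.637 | 36% |
| 30/70 | 0.348 | 0.759 | 0.576 | 42% |
| 20/80 | 0.280 | 0.700 | 0.490 | 51% |

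The documents give no cut-point, so the split is shown as a range.

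**3. What that means for power (illustration).** Use the Fisher z approximation, two-sided α 0.05: power ≈ Φ(atanh(r)·√(n−3) − 1.96). With n = 75, √72 = 8.485. Take r = 0.32, chosen so that the continuous analysis has about 80% power.

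| Exposure form | r | atanh(r)·8.485 | Power |
|---|---|---|---|
| Continuous | 0.320 | 2.814 | 0.80 |
| 50/50 | 0.255 | 2.215 | 0.60 |
| 30/70 | 0.243 | 2.102 | 0.56 |
| 20/80 | 0.224 | 1.933 | 0.49 |

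A simulation of 20,000 trials at n = 75, r = 0.318, agreed: 81% continuous, 61% at the median, 56% at 30/70.

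**4. Sensitivity.** At r = 0.30 and n = 75, power is 75% continuous against 54%, 50% and 44% after the three splits. If all 100 recruits were analysed at r = 0.30, it is 86% against 67%, 63% and 56%. The ordering and the rough size of the loss do not depend on the exact r.

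**The case against.** The strongest reply is that the labels may be loose synonyms. Only Section 2.10 sets out the stratification for analysis, and it names the instrument; the Abstract may restate it in everyday words. Groups are formed from baseline data, so their timing is fixed. A journal article may also leave the cut-point to a fuller document. All of this stands. The absence of a cut-point is not the point here, and movement of people between groups is possible but not shown.

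Some stronger readings are tempting but not supported:

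- *Sedentary means sitting time, so the two pairs rest on different accelerometer variables and would place many people differently.* Section 1 uses sedentarism as another word for physical inactivity, and no section names sitting time as an exposure. No reclassification count can be drawn from the text.
- *The correlation in Section 2.1 is a third, conflicting definition.* It is an additional analysis that can coexist with grouping. It also limits the loss, because activity appears to be used ungrouped for serum and cardiovascular markers.
- *The study's power falls from 80% to 60%.* The test behind 75 is unknown. If 75 was computed for groups, the planned 80% already refers to the grouped analysis.
- *The 150 min/week in Section 3 should be the cut.* There it describes "patients who were consistently meeting the minimum physical activity guidelines (150 min/week") in cited studies and is not offered as a grouping rule.

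The calculation is also a single-visit approximation for a three-visit design, and it assumes linearity. The sub-study comparator is a separate wording matter and moves nobody in the main cohort. None of this removes the core: the only model named works on groups, the exposure is continuous, and the two label pairs differ.

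**Conclusion.** The point holds as an avoidable loss of information combined with inconsistent labelling. Under a roughly linear relation and roughly normal activity, the two-group form loses at least about 36% of the information on activity, and about half if the split is 20/80. A true threshold effect would lose less. The power figures show the scale of the loss for one assumed association and say nothing about whether the planned 75 is adequate. The label mismatch is established by the text; its effect on who falls in which group is not. The loss falls on one of the two exposures in the main objective and is cheap to avoid, so the change is worth making before analysis.

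**What to change.** - In the Abstract and Section 2.10, state that baseline accelerometer activity enters the planned multilevel model as a continuous term, transformed or with a spline if it is skewed or the relation is curved.
- If a two-group split is kept, use it for description only, give it one label pair in both places, and fix its definition before outcomes are seen.
- Use one term for the sub-study comparator in the Abstract and Sections 2.1 and 2.3.

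The cost is a few wording edits and one changed model term, with no new measurements. The downside is small: a slope is less familiar to readers than a difference between two means, and its functional form has to be checked. The descriptive groups cover the first of these.

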## 3. Discussion

This protocol describes an ambitious follow-up study that will be conducted in adults previously infected with COVID-19 (before and after vaccination program), highlighting long-term consequences of COVID-19 and its correlation with physical activity, body composition, and cross-linked with vaccination in the Brazilian population. Our hypothesis links reduced visceral adipose tissue deposits (which exhibit an anti-inflammatory profile, as hypoleptinemia and hyperadiponectinemia) with higher physical activity levels as central factors in reducing the severity of SARS-CoV-2 aggression, promoting metabolic programming of immune cells (favoring anti-inflammatory response), protecting the cardiovascular system, and general clinical profile.

Patients with COVID-19 who were consistently inactive and malnutrition had a greater risk of hospitalization, admission to the ICU, and death due to COVID-19 compared with patients who were consistently meeting the minimum physical activity guidelines (150 min/week) [27,47,48]. Longitudinal cohort studies of individuals who developed severe COVID-19 are being conducted to investigate possible symptoms and long-term clinical and functional alterations [49,50]. Longitudinal follow-up studies reporting persistent symptoms and sequelae of COVID-19 in mild and moderate patients are also needed in order to understand the intrinsic physiological mechanisms involved in these processes, their potential protective factors, and public health policies needed for treatment in the post-pandemic period in order to substantially minimize long-term chronic sequelae.

In addition to investigating an overlooked population, one advantage of the study proposed here is that we will conduct comprehensive symptom and clinical assessments of long-COVID manifestations pre- and post-vaccination. Potential limitations include the fact that we will rule out the presence of current re-infection based only on the absence of clinical signs and symptoms, rather than on the basis of a negative RT-PCR test. We will also only assess a specific, young population.

In summary, studies seeking solutions to problems associated with the long-term consequences of COVID-19 are of great interest worldwide. Since this follow-up study will be conducted over several months, preliminary data analysis may encourage our team and other researchers to conduct interventional clinical trials targeting specific long-term manifestations of COVID-19. Finally, we hope that the clinical information fed back to the participants involved in this research will facilitate their access to healthcare.

### Limitations

In cases of the COVID-19 re-infection, this condition will be reported, and we will put major attention to the results. The patient will be considered an outlier and may be removed from the analysis.

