### 2.1. Study Design and Setting

A study design summary displaying the steps and evaluations of potential participants over approximately 18 months of follow-up is provided in Figure 1.

A follow-up period of approximately 18 months will be implemented. The procedures will be conducted for all participants at baseline, 6 weeks after vaccination, and 12 months after vaccination. After approval by the local Research Ethics Committee, patients previously infected with COVID-19 will be contacted to participate in the study through the local media and via electronic access to the participants’ database of Municipal Health Secretariat (MHS) of Presidente Prudente—São Paulo. Male and female patients aged 20–40 years with mild or moderate clinical COVID-19 infection will be recruited (intensive care cases will be excluded). An age-matched healthy control group that is negative for SARS-CoV-2 will also be enrolled. To detect previous SARS-CoV-2 infection, a lateral flow test for IgM and IgG antibodies will be conducted using internal anti-SARS-CoV-2 IgG and IgM ELISA kits. Participant exclusion criteria will include (1) presence of chronic non-communicable diseases, (2) smokers, (3) history of drug use, (4) medications such as anti-inflammatory drugs or antibiotics, (5) and frequent alcohol consumption (more than three times a week.

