### 2.3. Blood Collection and Analysis

At each time-moment, participants will visit the laboratory after overnight fasting. Forty milliliters of blood from an antecubital vein will be collected in a tube containing EDTA. To detect previous SARS-CoV-2 infection, a lateral flow test for IgM and IgG antibodies will be performed using internal anti-SARSr-CoV IgG and IgM ELISA kits. All patients (infected and non-infected with SARS-CoV-2) will be evaluated before (without vaccine) and after (with vaccine) the vaccination program. We plan to follow up the calendar vaccination of the São Paulo Government and recruit patients according to this schedule. Please, access information about the São Paulo State vaccination calendar in the link (https://www.prefeitura.sp.gov.br/cidade/secretarias/saude/vigilancia_em_saude/doencas_e_agravos/coronavirus/index.php?) (accessed on 5 January 2021). Phenotypes of immune cells will be characterized using multicolor flow cytometry, and monocytes, T cells, and Natural Killer (NK) cell subsets in whole blood will be quantified and characterized. T lymphocytes will be identified based on their positivity for CD3 and typical light scatter. Among positive CD3 cells, CD4^+^ T and CD8^+^ T cell subsets will be quantified. Based on the expression of CD14 and CD16, the classical (CD14++CD16−), intermediate (CD14++CD16+), and non-classical (CD14^+^CD16^++^) monocytes will be quantified. The NK cells will be defined as CD3^−^CD56^+^, and the two major subsets of NK cells, CD56^hi^CD16^−^ (CD56^bright^) and CD56^lo^CD16^+^ (CD56^dim^), will be identified. Biochemistry assays, including measurements of non-ester fatty acid (NEFA), glucose, triacylglycerol, total cholesterol, and HDL-c will be analyzed using a colorimetric method. Cortisol, insulin, and apolipoprotein A1 concentrations will be analyzed using ELISA. To determine the inflammatory status of the participants, the plasma concentrations of IL-1β, IFN-α, IFNγ, TNF-α, MCP-1, MIP-1β, IL-8, IL-10, IL-12p70, IL-17A, IL-18, IL-23, IL-33, IL-1ra, IL-2, IL-6 will be measured using the LUMINEX method.

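### Re-infected participants may be removed at discretion as outliers, and controls infected during follow-up have no rule; both can bias the main contrasts

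*Protocol article*

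**What the plan says.** The rule stands under Limitations, after the Discussion. Its first sentence is a reporting commitment: "In cases of the COVID-19 re-infection, this condition will be reported, and we will put major attention to the results". The second is the analysis rule: "The patient will be considered an outlier and may be removed from the analysis". The unit removed is the patient, and removal is optional.

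Four other places bear on it:

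- **Detection.** The Discussion lists as a limitation that "we will rule out the presence of current re-infection based only on the absence of clinical signs and symptoms", rather than on a negative RT-PCR test.
- **Grouping.** The Abstract states: "Using the baseline information, participants will be grouped based on physical activity levels", and names body composition and SARS-CoV-2 status as the other grouping factors. Section 2.1 adds: "An age-matched healthy control group that is negative for SARS-CoV-2 will also be enrolled".
- **Follow-up.** Section 2.1: "The procedures will be conducted for all participants at baseline, 6 weeks after vaccination, and 12 months after vaccination", over about 18 months in total.
- **Access to results.** Section 2.8 gives the research groups data for interim as well as final analyses, and the end of the Discussion expects preliminary analysis while follow-up continues.

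No sentence covers a first infection in a control after enrolment.

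**The concern.** An outlier is a suspect value. A re-infection is a genuine event that happens after the groups are formed and may act on the inflammatory and clinical outcomes being measured. Removing people because of it selects the analysis set on something that may depend on the exposure.

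The document gives a reason to expect such dependence. Its hypothesis in the Discussion is that less visceral fat and more activity reduce the severity of the infection. If so, re-infections in active, lean participants would tend to be mild and could pass unnoticed where detection rests on symptoms, while those in sedentary or high-fat participants would be noticed and become removable. This could happen even if the true re-infection rates were equal.

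Three features of the rule add to the problem. It is discretionary, and interim results may be known when the choice is made. It removes the whole person, so valid visits before the re-infection are lost. It is also one-sided: a previously infected participant with a new infection may be dropped, while a control with a new infection has no rule and, on the baseline grouping, remains a control. The activity, body-composition and infection-status contrasts are the ones exposed.

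**Working it through.** **Inputs from the document.** Optional removal of re-infected patients (Limitations); groups set from baseline information (Abstract); three visits over about 18 months (section 2.1); 75 participants estimated and 100 recruited, the surplus being for dropout (section 2.10).

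**Inputs not in the document, assumed here.** The re-infection rate, its relation to activity, its effect on outcomes, and the rate of first infection in controls.

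**1. The plan's own figures.** 75 / (1 - 0.25) = 100, so the surplus amounts to a 25% dropout allowance. The 75 cannot be checked, because section 2.10 does not state the test, effect metric, number of groups or within-person correlation. Some repeated-measures settings give it (for example f = 0.25, three visits, eight groups, correlation 0.3, interaction test). No stated figure is contradicted. There is no figure for re-infection.

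**2. Effect of removal on the activity contrast.** Let A = 1 for active, U be a shared cause of infection and outcome (SD 1), and R be a re-infection that triggers removal:

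- logit P(R) = log(0.25/0.75) + log(OR)·A + g·U
- Y = -0.5·A + U + h·R

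Simulated with 2,000,000 people per setting; the contrast is active minus sedentary, in SD of U:

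| OR | g | h | R active / sedentary | everyone kept | R removed |
|---|---|---|---|---|---|
| 1 | 0.5 | 0.5 | 26.1% / 26.1% | -0.499 | -0.501 |
| 0.5 | 0 | 0 | 14.2% / 25.0% | -0.500 | -0.500 |
| 0.5 | 0 | 0.5 | 14.3% / 24.9% | -0.555 | -0.502 |
| 0.5 | 0.5 | 0 | 15.3% / 26.0% | -0.499 | -0.449 |
| 0.5 | 0.5 | 0.5 | 15.3% / 26.1% | -0.553 | -0.449 |

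The first two rows show no shift when R is unrelated to activity, or unrelated to the outcome. In the third row removal deletes the part of the contrast that runs through re-infection: 0.5 × (0.249 - 0.143) = 0.053. In the fourth row the shift of 0.05 is selection through the shared cause. In the last row the two add up: 0.553 - 0.449 = 0.104. There the result after removal is neither the total contrast (-0.55) nor the direct effect (-0.50).

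**3. Controls infected during follow-up.** If a share q of controls is infected and shifts fully to the infected group's mean, the contrast becomes d × (1 - q). For d = 0.5, 50 per group (100 split equally, an assumption) and a two-sided 5% test:

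| q | contrast | power |
|---|---|---|
| 0 | 0.50 | 0.705 |
| 10% | 0.45 | 0.614 |
| 20% | 0.40 | 0.516 |
| 30% | 0.35 | 0.417 |

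A partial shift gives less dilution.

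**4. Numbers lost.** Only previously infected participants can be re-infected. If they are half of 75 completers (assumption), removal of a share p of them leaves 75 - 37.5p: 71 at 10% and 64 at 30%. If dropout is below 25%, more remain: 10% dropout and 15% removal across all 100 leave 100 × 0.90 × 0.85 = 76.5.

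**The case against.** The strongest case against has four parts.

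**The bias is conditional.** This is correct. A reader might infer that the study hypothesises protection against infection, so that removal must bias the result. The document does not say so. The Discussion's hypothesis concerns severity, and the Background treats protection against SARS-CoV-2 infection as unknown. The route that the text supports is differential detection through severity, and that is a possibility, not a demonstrated fact.

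**Setting a second infection aside can be a legitimate aim.** The study asks about the long-term course after one mild to moderate infection. That is fair, but it would call for a fixed rule that keeps the earlier visits, not optional removal of the person. The same reasoning rules out an easy remedy: entering later infection as a time-varying covariate in the primary model conditions on the same post-baseline event.

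**The control problem is inferred.** This is also correct. It follows from baseline grouping and from a rule confined to re-infection, and a condensed article may leave such detail to a fuller document. It is therefore the secondary part of this point.

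**Detection may be better than it seems.** The sentence in the Discussion is about current re-infection and says nothing of how infections between visits are found. Section 2.3 describes antibody testing ("To detect previous SARS-CoV-2 infection, a lateral flow test for IgM and IgG antibodies will be performed"). A reader might infer that such a test is uninformative once both groups are vaccinated. The article gives neither the assay's target antigen nor the vaccines, so that cannot be claimed.

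None of this defends the removal sentence itself, which is a stated rule and not an omission.

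**Conclusion.** The point holds in a limited form. The rule treats a real post-baseline event as an outlier and leaves removal of the whole person open to choice, possibly after interim results are known. It can bias the activity and body-composition contrasts if detected re-infection is related to those exposures and to the outcome. The activity contrast is not biased if detected re-infection is unrelated to activity. By inference, controls infected later keep their baseline label, which can dilute the infection-status contrast.

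The size is not derivable from the document. As illustrations only: in the least favourable setting simulated, a contrast of -0.55 SD fell to -0.45 SD; with 10–30% of controls infected and fully shifted, the status contrast lost 10–30% and power at d = 0.5 fell from 0.71 to between 0.61 and 0.42.

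A reader might also infer that removals must push the analysis set below 75. That would require dropout to use up nearly all 25 spare places, and no expected dropout rate is stated beyond the allowance implied by recruiting 100. The reason to change the rule is its form, not a proven loss of power.

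**What to change.** 1. Delete the sentence that labels re-infected participants outliers and permits their removal. Keep the commitment to report re-infections.
2. State that the primary analysis keeps all participants and all visits, by baseline group, without adjustment for infection after baseline.
3. Record the date of every new infection in both groups, whether a re-infection or a first infection in a control, from the visit interview and the municipal health database.
4. Pre-specify one sensitivity analysis, identical for previously infected participants and controls, that keeps visits before a new infection and censors only later ones. Censoring also selects on the event, which is why it belongs here and not in the primary analysis.

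The cost is a change of wording, a dated question at each visit and a repeat database look-up. Section 2.1 describes database access for recruitment, so its use for follow-up, including for controls, should be confirmed. The statistical price is slightly more heterogeneity at the late visits. The change should be made before any interim results are examined.
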